#### Primary outcome

The primary outcome indicator is patient exercise adherence. We will use the Exercise Adherence Scale developed by Weng (35) to assess patients’ exercise adherence. The scale contains 15 entries divided into three dimensions covering exercise adherence, exercise monitoring adherence, and actively seeking advice. The higher the total score of the scale, the better the patient’s exercise adherence.

#### Secondary outcomes

Secondary outcome indicators include willingness to exercise, fear of exercise, exercise self-efficacy and quality of life. The specific assessment tools are listed below:

Willingness to exercise: Willingness to exercise will be measured using the 3-item questionnaire used in the van‘t Riet et al. (36) study. Higher scores indicate a greater willingness to exercise in patients.Exercise fear: Exercise fear will be measured by the Tampa Scale for Kinesiophobia Heart (TSK-Heart) (37), which consists of 15 items covering four dimensions: fear of injury, functional deterioration, exercise avoidance and perceived cardiac risk. The total score of the scale ranges from 15 to 60, with higher scores indicating greater exercise fear, and a total score of ≥37 being defined as high exercise fear.Exercise self-efficacy: Exercise self-efficacy will be measured by the Cardiac Exercise Self-Efficacy Instrument (CESEI) (38), which consists of 16 items with a total score of 80. The higher the score, the greater the patient’s sense of cardiac exercise self-efficacy.Quality of life: Quality of life will be measured using the Chinese cardiovascular quality of life questionnaire (CCQQ) for cardiovascular disease patients (39). The questionnaire is based on the definition of quality of life by the World Health Organization (WHO) and assesses the level of quality of life of patients from three aspects: physical, psychological and social. It is the first universal scale used for quality of life evaluation of patients with cardiovascular disease in China. The CCQQ scale consists of 6 dimensions, covering physical strength, medical condition, medical situation, daily situation, psychosocial and work situation, with 24 entries and a total score of 0–154 points. The scores are divided into the following levels: 0–68 indicates poor quality of life, 68–84 is average, 84–120 is moderate, and 120–154 is excellent quality of life. The questionnaire has been widely used in China to evaluate the quality of life of patients with cardiovascular diseases.

### Data statistics and analysis

Statistical analysis of the data will be performed using SPSS 25.0 and R 4.3.2 software. All statistical analyzes will be conducted using two-sided tests, with a significance level set at *p* < 0.05. Continuous variables will be described using mean ± standard deviation, while categorical variables will be expressed as frequency (n) and percentage (%). For intergroup comparisons of baseline data: continuous variables that follow a normal distribution will be compared using one-way analysis of variance (ANOVA); those that do not follow a normal distribution will be compared using the Kruskal–Wallis nonparametric test. Categorical variables will be compared using the chi-square test or Fisher’s exact test, as appropriate.

To comprehensively analyze changes in outcome indicators across different groups and time points following the intervention, data will be analyzed using a linear mixed-effects model (LMM). The gain-loss framing, narrative framing, and time will be included as fixed effects, while individual study participants will be included as random effects to account for individual variability. The LMM model will be constructed to assess the main effects of the gain-loss framing, narrative framing, and time, as well as their interaction effects. If the interaction effects are significant, further analysis of the simple effects of the message framing and time will be conducted to explore the impact of the intervention on outcome indicators at different time points. If interaction effects are not significant but main effects are, Tukey’s HSD *post hoc* comparison analysis will be further conducted to explore the independent effects of different message framing and time points on outcome indicators. The LMM model uses maximum likelihood estimation and is able to fit the model efficiently using all available data containing missing values, and is therefore robust to missing data.

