### Sample size

The primary outcome indicator adopted in this study is exercise adherence. The sample size was calculated using the sample size estimation formula for multiple means in randomized controlled trials, accounting for a 20% dropout rate, resulting in a final sample size of 100 subjects. The sample size calculation was determined using PASS 2021 software.

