### Randomization, allocation, and blinding mechanisms

This study employs a computer-generated simple randomization method. Before the trial, a researcher will use computer software to randomly generate a randomization number list, allocating patients to four groups in a 1:1:1:1 ratio: Group A (gain-narrative framed message), Group B (loss-narrative framed message), Group C (gain-framed non-narrative message), and Group D (loss-framed non-narrative message). The generated random number list will be stored in a sealed envelope until the randomization process is completed. The researcher responsible for generating the random sequence will not participate in the patient recruitment process.

This study will be blinded to the participants, who received the educational video via WeChat. During this process, patients will not be aware of which message-framed video they received. Meanwhile, the video interventions in the four groups will be designed to mask the content of the different screens through similar designs (such as textual descriptions, animations combined with case presentations), and the researchers will personalize reminders and instructions based on patients’ responses during the experiment, and will process the feedback through a standardized template to avoid disclosing the group characteristics and to ensure the effectiveness of the interventions. Unblinding may be performed during the trial when essential to ensure participant safety or to facilitate necessary therapeutic adjustments in the event of a serious adverse event to minimize any potential impact on study outcomes, as reported by the participant or as assessed by the study investigators and the treating physician. If unblinding is required during the trial, the reasons, timing, participant-related information, and the corresponding decision-making process will be fully documented and archived. All unblinding procedures will adhere to ethical standards.

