### Data collection and outcomes

Data will be collected at baseline before intervention, 1-month post-intervention, and 3-month post-intervention. At baseline, paper questionnaires will be distributed on the day of discharge before the first video viewing to collect data; at 1-month and 3-month follow-up, online questionnaires will be completed via Questionnaire Star. For those unable to complete the survey via Questionnaire Star, telephone follow-ups will be conducted. The questionnaires will be distributed and collected by trained researchers. The assessment tools used need to be fully validated and selected for their established reliability and validity in the original study, ensuring accuracy and comparability. In the process of completing the questionnaire, the researcher will answer the subjects’ questions on time, check for missing items after completing the questionnaire, and instruct the subjects to add a message as needed. After data collection is completed, the data will be entered promptly. Following data entry into the analysis system, independent double data checks will be performed by two researchers to ensure accuracy. This trial is a low-risk, non-pharmacological behavioral intervention; therefore, a formal DMC will not be established.

The assessment of general patient message, designed by the study team itself through literature review and group discussion, will be divided into 2 parts. Part 1 will be general demographic message, including gender, age, ethnicity, religious beliefs, literacy, marital status, mode of residence, occupation, monthly household income, and type of health insurance; part 2 will be disease-related information, including duration of coronary heart disease, current diagnosis, medication use and types of medication, comorbidities, and a history of acute myocardial infarction or cardiac surgery.

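### The stated mixed model (maximum likelihood, participant as the only random term) can give standard errors for frame-by-time contrasts that are too small or too large; unstructured REML avoids this at almost no cost

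*Protocol article*

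**What the plan says.** Under Data statistics and analysis, the article describes one model for all outcomes. On the fixed part: "The gain-loss framing, narrative framing, and time will be included as fixed effects". Its purpose is to "assess the main effects of the gain-loss framing, narrative framing, and time, as well as their interaction effects". On the random part: "individual study participants will be included as random effects to account for individual variability". No random slope and no residual covariance structure is named. On estimation: "The LMM model uses maximum likelihood estimation", a choice the article explains by the wish to use incomplete records. Testing is by "two-sided tests, with a significance level set at *p* < 0.05". Simple effects are examined only after a significant interaction.

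Under Data collection and outcomes, measurements are taken at "baseline before intervention, 1-month post-intervention, and 3-month post-intervention". Baseline is a paper form completed on the day of discharge; the follow-ups are online, or by telephone where needed.

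**The concern.** A participant random intercept makes the variance equal at every visit and the correlation equal between every pair of visits. Here baseline precedes the first video and home exercise, and differs in mode from the two later visits, which are two months apart. Equal correlation and equal spread across such visits is a strong assumption, and the article does not defend it.

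The model estimates one average within-person variance and uses it for every change. If changes truly differ in variance, some contrasts get intervals that are too narrow and others intervals that are too wide. Whether a framing effect appears, and whether it lasts, rests on these contrasts, including those for the primary outcome. Maximum likelihood adds a smaller problem: it makes no allowance for the estimated group means, so it understates the variance.

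**Working it through.** **Inputs from the article.** 100 participants ("accounting for a 20% dropout rate, resulting in a final sample size of 100 subjects"), four groups ("allocating patients to four groups in a 1:1:1:1 ratio"), three visits, two-sided 5%, maximum likelihood. The dropout step can be reproduced: 80 / (1 - 0.20) = 100, so 80 completers, 20 per group.

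**Assumptions.** Random intercept; full 2 x 2 x 3 fixed part; complete data on 80; normal critical value 1.96 (the article names no degrees-of-freedom method). Correlations and SDs are not in the article, so ranges are used.

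**Step 1: maximum likelihood alone.** With four group means per visit, the SE of a within-person contrast is multiplied by sqrt((N - 4)/N).
- N = 80: sqrt(76/80) = 0.975, so the real error is 2 x (1 - Phi(1.96 x 0.975)) = 0.056.
- N = 100: sqrt(96/100) = 0.980, so the real error is 0.055.

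SEs are 2-2.5% too small, in one direction only.

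**Step 2: single frame-by-time contrasts.** The model variance of any change is 2 x (mean variance - mean covariance). The true variance is S_ii + S_jj - 2 S_ij. The SE ratio is 0.975 x sqrt(model / true), and the real error is 2 x (1 - Phi(1.96 x ratio)).

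Example, correlations 0.4 (baseline-1m), 0.3 (baseline-3m), 0.7 (1m-3m), SDs equal to 1: mean covariance (0.4 + 0.3 + 0.7)/3 = 0.467; model variance 2 x (1 - 0.467) = 1.067.
- Baseline-3m: true variance 2 - 0.6 = 1.40; ratio 0.975 x sqrt(1.067/1.40) = 0.851; error 9.5%.
- 1m-3m: true variance 2 - 1.4 = 0.60; ratio 0.975 x sqrt(1.067/0.60) = 1.300; error 1.1%.

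| Assumed correlations (baseline-1m / baseline-3m / 1m-3m) and SDs | SE ratio, same order | Real error, same order |
|---|---|---|
| 0.5/0.5/0.5, equal SDs | 0.975 / 0.975 / 0.975 | 5.6% / 5.6% / 5.6% |
| 0.6/0.5/0.6, equal SDs | 1.014 / 0.907 / 1.014 | 4.7% / 7.5% / 4.7% |
| 0.6/0.36/0.6, equal SDs | 1.068 / 0.844 / 1.068 | 3.6% / 9.8% / 3.6% |
| 0.4/0.3/0.7, equal SDs | 0.919 / 0.851 / 1.300 | 7.2% / 9.5% / 1.1% |
| 0.5/0.5/0.5, SDs 1.0/1.2/1.4 | 1.074 / 0.958 / 0.912 | 3.5% / 6.0% / 7.4% |

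Simulation of the four equal-SD rows (20,000 trials each) agrees to within about 0.3 percentage points. In the last row the 1m-3m contrast is too liberal, where the equal-SD rows with unequal correlations make it nominal to conservative.

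**Step 3: frame effect at 3 months.** The model uses the mean variance in place of the 3-month variance.
- Equal SDs: the two coincide, and only the ML factor remains (about 5.6%).
- SDs 1.0/1.2/1.4: mean (1 + 1.44 + 1.96)/3 = 1.467 against 1.96; ratio 0.975 x sqrt(1.467/1.96) = 0.843; error about 10%.
- SDs 0.7/1.0/1.2: mean (0.49 + 1 + 1.44)/3 = 0.977 against 1.44; ratio 0.80; error about 12%.

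**Step 4: the planned sequence.** Steps 2 and 3 test each contrast on its own. In simulation at N = 80, the overall frame-by-time test under random-intercept ML has an error of about 6.0-6.8%. Exact equal correlation already gives about 6%, so misspecified covariance adds under one point. Requiring that test to be significant first brings baseline-3m (0.4/0.3/0.7, equal SDs) to about 5.6% and the 3-month frame effect (SDs 0.7/1.0/1.2) to about 3.9%.

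**Step 5: does the remedy work?** REML with a random intercept does not cure the covariance part: with 0.6/0.36/0.6 it still gives about 3.2% / 8.8% / 3.2%. Unstructured REML with a t or F reference held about 5% in every scenario.

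**The case against.** The article nowhere says that the random part is an intercept only. It refers to a full protocol and analysis plan in the trial registry, where covariance structure and degrees of freedom are commonly settled. That stands as a caution: the random intercept is the natural reading, not the literal text. It does not remove the point, because the article positively states maximum likelihood and names a single random term.

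A reader might infer that the error bars of this trial are wrong in both directions. The article does not support that. It gives no SDs or correlations, and under equal variances and correlations the random-intercept covariance is correct. Nor does it support the claim that the 1-to-3-month contrast is always too conservative, or that 3-month effects are always declared too often; Steps 2 and 3 show that both depend on the assumptions.

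It is also fair to object that ungated error rates are not those of the planned procedure, and that time-averaged framing effects are untouched by the covariance choice in balanced data (5.5-5.9% in every scenario, the ML effect alone). Both objections stand. The gate was checked for one frame-by-time interaction only, and other significant interactions could also open simple effects. The gate also leaves the reported SEs and confidence intervals of single contrasts uncorrected.

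**Conclusion.** The point holds in a limited, conditional form. On its natural reading, the stated model can misstate the precision of single frame-by-time contrasts in either direction. The sizes rest on the assumed correlations and SDs, 80 complete cases and a large-sample reference. Within the planned sequence the inflation is modest. Maximum likelihood is a minor contributor to single-contrast error, but it accounts for most of the excess in the overall test. This is a worthwhile improvement to make before analysis, not evidence that the planned results would be invalid.

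**What to change.** Replace the stated model with a repeated-measures linear model having the same fixed effects, an unstructured 3 x 3 covariance over the visits, REML estimation, and Kenward-Roger or Satterthwaite degrees of freedom. Keep maximum likelihood only for likelihood-ratio comparisons of fixed effects. REML is also likelihood-based and uses incomplete records, so the article's reason for choosing maximum likelihood is still met. If the registered analysis plan already specifies this, align the article's wording with it.

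The cost is one sentence and no new data. The small downside is four more covariance parameters (six instead of two), which 80-100 participants can support. With complete data, each change contrast becomes an exact t-test on 76 degrees of freedom.

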## Discussion

### Limitations of the literature and strengths of the protocol

Existing literature on the relationship between message framing effects and health behavior has primarily focused on the role of single framing, neglecting the synergistic effects of different frame combinations. Additionally, there has been limited research on patients post-PCI, particularly regarding the application of narrative framing in exercise rehabilitation. The strength of this study lies in its pioneering integration of the gain-loss framing with the narrative framing, enabling a more comprehensive intervention strategy for patients after PCI through multi-dimensional assessment. Furthermore, the study employs a rigorous randomized and blinded design, minimizing bias and enhancing the internal validity of the results.

### Design justification and constraints

This study employs a 2 (gain vs. loss framing) × 2 (narrative vs. non-narrative framing) factorial design, which is relatively novel in the field of post-PCI patient exercise rehabilitation education. This design allows the researcher to test the independent effects of two or more factors at the same time, and more importantly, it can analyze whether there is an interaction effect between the different levels of these factors, i.e., whether the effect of one factor is dependent on the level of another factor. This means the design can not only obtain the message on the main effects of each factor, but also find out whether the factors act synergistically, antagonistically, or independently of each other, thus greatly improving the message output and experimental efficiency of the study, and avoiding the large amount of resources and time costs required to conduct single-factor experiments in multiple trials. It can further validate the unique value of the message framing effect in exercise rehabilitation education and provide new insights for future theoretical development in this field. The absence of a control group receiving conventional education means that we cannot directly determine if the message-framing interventions are superior to standard educational practices. To address this design limitation, this study strictly adopts a pre-post comparison format. Based on this, future studies may consider setting up a blank control group, where the control group receives routine exercise rehabilitation education without specific message framing interventions. By comparing the results of the intervention group with those of the blank control group, the effectiveness of the message framing intervention can be more accurately assessed, while eliminating other confounding factors, thereby enhancing the scientific rigor and reliability of the study conclusions.

As this is a single-center study conducted at a tertiary-level hospital in Zhejiang Province, the sample size is relatively small. This may result in certain regional limitations and insufficient sample representativeness, potentially limiting the generalisability of the study findings to patients in other regions or different types of hospitals. To enhance the external validity of the study results, future research could recruit more patients from multi-center, cross-regional studies, encompassing different types of healthcare institutions and social backgrounds, thereby providing a more comprehensive and accurate assessment of the impact of the message framing on post-PCI patient exercise rehabilitation.

During the implementation phase of the intervention, although we can remind patients to watch the video via WeChat or telephone, we still cannot guarantee that each patient has carefully watched all the video content, which may be a limitation.

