1 week after discharge	Aerobic exercise guidance	Gain frame	Loss frame	Gain frame	Loss frame	WeChat
2 Weeks after discharge	Resistance exercise guidance	Gain frame	Loss frame	Gain frame	Loss frame	WeChat
3 Weeks after discharge	Flexibility exercise guidance	Gain-narrative frame	Loss-narrative frame	Gain frame	Loss frame	WeChat

During the intervention period, patients in all four groups can continue to receive their regular medical treatment and rehabilitation management (e.g., medication, dietary adjustments, psychological support, etc.), which are assessed to be compatible with the intervention content of this trial and are not expected to affect the effectiveness of the intervention. If patients need to receive other treatments (e.g., surgery, emergency treatment, etc.) or adjust their routine treatment due to health problems during the trial period, the research team will assess whether these treatments affect the efficacy and credibility of the findings of the trial and decide whether participants can continue to participate in the study. In addition, any additional treatments or medications other than routine treatment will be reported to the research team in advance and will be evaluated by the research team as appropriate to ensure that they do not adversely affect the trial intervention.

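### A pre-post comparison does not make up for the missing conventional-education arm, so the time effect should not be read as programme effectiveness

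*Protocol article*

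**What the plan says.** The trial randomises by "allocating patients to four groups in a 1:1:1:1 ratio". All four groups receive videos, and none receives conventional education alone. The section Design justification and constraints draws the right consequence, that "we cannot directly determine if the message-framing interventions are superior to standard educational practices", and then offers a remedy: "To address this design limitation, this study strictly adopts a pre-post comparison format". It goes on to recommend a control group for future studies, on the ground that this would measure effectiveness more accurately and remove other confounding.

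The time points come from Data collection and outcomes: "Data will be collected at baseline before intervention, 1-month post-intervention, and 3-month post-intervention". For the first of these, "paper questionnaires will be distributed on the day of discharge before the first video viewing to collect data". Follow-up is by online questionnaire, with telephone for those who cannot use it.

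Under Data statistics and analysis, a linear mixed model is to "assess the main effects of the gain-loss framing, narrative framing, and time, as well as their interaction effects". If interactions are significant, simple effects of framing and time follow. If only main effects are significant, Tukey comparisons follow, and these are described as showing the separate effects of the frames and of the time points.

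**The concern.** The sentence credits the design with a property it does not have. The admitted gap is the lack of a concurrent comparison with conventional education. Measuring the same patients before and after does not supply one, because whatever else changes between discharge and follow-up changes in all four arms at once.

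What is at stake is interpretation. The article puts forward pre-post change as an answer to the control-arm problem, and the analysis section supplies a significance test for exactly that change. Together they leave room for a before-after finding to be presented with the authority of a randomised trial.

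**Working it through.** **What the common change contains.** The sources, by section:

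- Interventions and Table 2: every arm gets the same unframed first session at discharge. Reminders, questions and praise follow on the same schedule in all arms, and routine education in hospital and after discharge is identical.
- Interventions: "patients in all four groups can continue to receive their regular medical treatment and rehabilitation management".
- Implementation challenges and solutions: incentives and regular follow-up are described without distinction by arm.
- Data collection and outcomes: baseline is a paper form on the day of discharge; later forms are online or by telephone.
- Setting: patients are recovering after PCI over the whole interval.

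For any arm, therefore:

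mean change = video effect + recovery + routine care and education + contact, praise and incentives + change of collection mode + repeat-measurement effects.

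The main effect of time averages this sum over the arms. Only differences between arms remove the shared terms, and those differences estimate one frame against another. No contrast among the four arms isolates the video effect as a whole.

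**The plan's own figure.** The sample size section gives 100 patients including 20% dropout. The dropout step is consistent with 80 / (1 − 0.20) = 100. The article gives no effect size, SD or power, so the calculation cannot be followed further. The argument above does not depend on the sample size.

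**Illustration of how easily a shared drift becomes significant.** Inputs: n = 80 evaluable (back-calculated as above) and two-sided 0.05 (Data statistics and analysis). The pre-post correlation r is assumed to be 0.3 to 0.7, and the size of the drift is also assumed, because the article gives neither. One paired comparison stands in for the three-time-point mixed model.

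SD of change, in units of the outcome SD = √(2(1 − r)):

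- r = 0.3: √1.4 = 1.183
- r = 0.5: √1.0 = 1.000
- r = 0.7: √0.6 = 0.775

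The mean change detectable with 80% power, in units of the SD of change, is 0.317 for n = 80 from the noncentral t distribution. The normal approximation is close: (1.960 + 0.842) / √80 = 0.313. Multiplying by the SD of change:

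- r = 0.3: 0.317 × 1.183 = 0.375 SD
- r = 0.5: 0.317 × 1.000 = 0.317 SD
- r = 0.7: 0.317 × 0.775 = 0.246 SD

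Probability of a significant time effect when the videos do nothing and all arms share a drift:

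| Shared drift | r = 0.3 | r = 0.5 | r = 0.7 |
|---|---|---|---|
| 0 | 5% | 5% | 5% |
| 0.2 SD | 32% | 42% | 63% |
| 0.3 SD | 61% | 76% | 93% |
| 0.5 SD | 96% | 99% | nearly 100% |

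**Check on the randomised contrasts.** A simulation of the 2 × 2 change-score model used 20 patients per cell, a drift of 0.5 SD, r = 0.5, no framing effect and 10,000 runs. Time was significant in 99.3% of runs. Gain-loss by time was significant in 5.3%, narrative by time in 5.1% and the three-way interaction in 5.0%. The drift fills the time effect and leaves the framing contrasts at their nominal level.

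**The case against.** The strongest defence is that the article is open about the limitation. The sentence before the claim concedes the missing comparison, and the text after it recommends a control group and acknowledges residual confounding. That stands: nothing is concealed, and the fault lies in the claimed remedy.

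A reader might infer that the time effect will be reported as success. The documents do not support this. No section defines success by change over time or says it will be presented as superiority over standard education. Time is an ordinary fixed effect in a repeated-measures model. The reference in the analysis section to the intervention's impact at different time points applies only after a significant interaction, and it covers framing contrasts at a given time, which are randomised. Objective 2 speaks of differently framed education and can be read as comparative.

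A reader might also infer that adherence must rise whatever is shown, because baseline precedes any home exercise. This too is undocumented. The article gives no recall period for the adherence scale and does not require a first PCI, so some patients may have exercised before. The direction of change without the videos is unknown. The point needs only that the change is confounded.

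Finally, the power figures show that a before-after test can detect change, which is true of any such test. They do not measure damage to the randomised comparisons. That is correct, and they serve here as illustration only.

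None of this rescues the sentence itself. Nothing elsewhere in the article corrects it, and the Tukey step does treat time points as having effects of their own.

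**Conclusion.** The statement that a pre-post format addresses the absence of a conventional-education arm is wrong as written. This follows from the design and needs no numerical assumption. Combined with a tested main effect of time, it leaves open a causal reading of an uncontrolled change. Whether anyone would make that reading is not something the article settles.

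The size is illustrative: a shared drift of roughly 0.25 to 0.38 SD, with no framing effect, would make time significant with 80% power. This rests on 80 evaluable patients, an assumed correlation between 0.7 and 0.3, and a single paired test. The randomised gain-loss, narrative and interaction contrasts are not affected.

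**What to change.** 1. Design justification and constraints: delete the sentence, or replace it with a statement that the trial estimates differences between frames and that change from baseline cannot substitute for a conventional-education control.
2. Data statistics and analysis: state that the main effect of time and within-arm changes are descriptive and are not evidence that the programme is effective. Omitting their p-values is optional.
3. Objective, second item: word it as the relative effectiveness of the frames, and confine effectiveness conclusions to the framing and framing-by-time contrasts.

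This changes wording only, with no added patients, visits or arms. The price is a narrower claim: the trial can say which frame does better, but not whether the programme works.
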